The secondary endpoints include: (1) the proportion of patients with normokalemia (serum potassium 3.5-5.0 mmol/L) at each onsite visit; (2) the proportion of patients achieving RAASi optimization with normokalemia at weeks 12 and 24; (3) the percentage change in urinary albumin-to-creatinine ratio (UACR) from baseline to weeks 48 and 96 among patients receiving RAASi at baseline; (4) the proportion of patients experiencing severe hyperkalemia (serum potassium > 6.5 mmol/L) during the 96-week intervention period; (5) medication possession ratio (MPR) for hyperkalemia therapies, defined as the number of days hyperkalemia medication was used between two onsite visits divided by the total number of days between those visits, assessed at each onsite visit; (6) time to first hyperkalemia recurrence; (7) hospital-level hyperkalemia management status at baseline and at weeks 48 and 96; (8) time to first occurrence of any component of the kidney-specific composite endpoint, defined as sustained eGFR decline ≥ 50%, ESRD, or renal death; (9) eGFR slope over the 96-week follow-up period; (10) time to first occurrence of any component of the heart-specific composite endpoint, including rehospitalization for heart failure (rhHF), worsening heart failure, emergency room visits, or cardiovascular death; (11) time to first occurrence of arrhythmia; (12) frequency of serum potassium testing and number of hyperkalemia episodes during the first 48 weeks of intervention (onsite and remote visits), with hyperkalemia defined as serum potassium > 5.0 mmol/L and multiple measurements within 48 h counted as a single episode; (13) the proportion of patients requiring emergency department visits, emergency dialysis, or hospitalization during the 48-week intervention period; (14) safety and clinical assessments, including adverse events (AEs), serious adverse events (SAEs), adverse drug reactions (ADRs); (15) vital signs; (16) physical examination findings; (17) clinical laboratory parameters; and (18) electrocardiographic assessments.

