### Timeline of the study

The schedules of study activities for patients and participating sites are summarized in Tables 1 and 2, respectively. Patient enrollment will commence only after completion of comprehensive guideline-directed medical therapy training for HCPs at both the study-wide and individual site levels. The screening period will extend from 14 days to 1 day prior to enrollment. Following enrollment, patients will receive individualized treatment plans and hyperkalemia management strategies determined by their HCPs, including disease education, self-management materials, prescriptions for RAASi, serum potassium monitoring, and potassium-lowering therapies as appropriate. The maximum duration of follow-up will be 96 weeks. After the baseline visit and initial data collection, each participant will attend six scheduled onsite visits at weeks 12, 24, 36, 48, 72, and 96 post-enrollment. Patients who discontinue participation prematurely will be invited to complete an early withdrawal visit. During intervals without scheduled onsite visits, participants will undergo remote follow-up every 4 weeks. Patients will be considered to have completed the study upon completion of the 96-week follow-up, death, or study termination. The study end date is defined as the date of the final visit of the last enrolled patient.

**Table 1 Tab1:** Schedule of activities for patients

Procedure	Screening period	Management period/follow up^a^							Early Withdrawal + 14 day^c^
Visit ^b^	Day − 14 ~ Day-1	Day 0 Baseline *	Week 12 ± 14 days	Week 24 ± 14 days	Week 36 ± 14 day	Week 48 ± 14 days	Week 72 ± 28 days	Week 96 ± 28 days	
	/	V0	V1	V2	V3	V4	V5	V6	
Informed consent	X								
Inclusion and exclusion criteria	X	X							
Demographics ^d^	X								
Medical history ^e^	X								
Physical examination ^f^	X		X	X	X	X	X	X	
Height, weight	X	X	X (weight only, if available as per clinical practice)						
Laboratory tests (Hematology, Clinical Chemistry, Urinalysis)	X^g^		X	X	X	X	X^h^	X^h^	X^i^
12-lead ECG ^j^	X	X	X	X	X	X	X	X	X
Vital signs ^k^	X	X	X	X	X	X	X	X	
Patient’s daily checklist release and/or retrieve		X	X	X	X	X	X	X	X
RAASi treatment pattern ^l^		X	X	X	X	X	X	X	X
Hyperkalemia treatment pattern ^m^		X	X	X	X	X	X	X	X
Concomitant medication ^n^	X	X	X	X	X	X	X	X	X
Clinical progression/medical events collection			X						X
Administration of study intervention		X	X •Patient education at each onsite visit •Patient self-learning						
AE/SAE^p^	X								X

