HCP, health care professional; BP, blood pressure; eGFR, estimated glomerular filtration rate; ECG, electrocardiogram; RAASi, renin-angiotensin-aldosterone system inhibitor; UACR, urinary albumin/creatinine ratio; ESRD, end-stage renal disease; rhHF, rehospitalization for heart failure; HF, heart failure; ER, emergency room; CV-death, cardiovascular death; AE, adverse event; SAE, serious adverse event; ICF, informed consent form; MAH, marketing authorization holder

a. Day 0 refers to the day on which the patient is enrolled

b. Remote visits: Telephone calls will be conducted every 4 weeks (± 7 days) following enrollment if no onsite visit occurs, to review patient self-management and assess adherence. Patients will also be reminded to follow their HCP’s advice regarding serum K⁺ testing, medication adherence, dietary restrictions, etc

c. Early withdrawal visits will be conducted for patients who discontinue early, preferably within two weeks of withdrawal confirmation. These visits may be onsite or remote

d. Demographic data include gender, age, race, and ethnicity

e. Medical history includes comorbidities and relevant conditions requiring medication within 1 year prior to enrollment

f. Physical examination: A complete physical examination will be performed at V0 (Day 0). A brief physical examination will be conducted during follow-up visits. A complete physical examination includes assessment of general appearance; respiratory, cardiovascular, abdominal, skin, head and neck (including ears, eyes, nose, and throat); lymph nodes; thyroid; musculoskeletal (including spine and extremities); and neurological systems. A brief physical examination includes assessment of at least the neurological system, skin, lungs, cardiovascular system, abdomen (liver and spleen), and lymph nodes

g. The serum K⁺ test must be completed within 48 h prior to enrollment. Other laboratory test results within 14 days before baseline may be accepted

h. At weeks 72 and 96, only hematology, urinalysis, renal function (eGFR), blood electrolytes (Na⁺/K⁺/Cl⁻), and UACR will be assessed. Additional laboratory tests may be collected if available per routine clinical practice

i. At early withdrawal visits, only renal function (eGFR) and serum K⁺ will be tested. Additional laboratory assessments may be performed if available per clinical practice

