j. Additional ECGs may be performed if available as per clinical practice. ECG results obtained within 14 days prior to baseline may be used as screening data

k. Vital signs include body temperature, systolic and diastolic blood pressure, pulse rate, and respiratory rate

l. RAASi treatment patterns include whether therapy was initiated and, if so, detailed data (drug/treatment name, usage and dosage, frequency, start and end dates, any changes or interruptions, and reasons for discontinuation, if applicable)

m. Hyperkalemia treatment: Pharmacological treatment includes whether therapy was administered and, if so, treatment name, usage and dosage, frequency, start and end dates, and any changes or interruptions with reasons (if applicable). Non-pharmacological treatment includes treatment name, start and end dates, and reason for change or interruption (if applicable)

n. Concomitant medications will be collected throughout the study. Blood pressure and RAASi treatment in the 3 months prior to enrollment will also be recorded. For patients continuing RAASi treatment during screening, the date of the last dose prior to enrollment should be documented

o. Clinical progression/medical events include: Kidney-specific composite events: sustained eGFR decline ≥ 50%, ESRD, or renal-related death. Cardiovascular-specific composite events: rhHF, worsening HF, emergency room visit, or cardiovascular death. Other events: arrhythmia, hospitalization, emergency dialysis, emergency department visit, and death due to other causes

p. Adverse events (AEs): All AEs and SAEs related to potassium binders, as well as special situations (e.g., medication error, drug abuse, misuse, and pregnancy) involving LOKELMA^®^, will be actively collected. The collection period spans from the time of ICF signing (for patients using a potassium binder prior to enrollment) or the date of treatment initiation (for those starting after enrollment) until 24 h post-discontinuation. AEs involving other products for which AstraZeneca is not the marketing authorization holder (MAH) will be reported spontaneously to the respective MAHs

* Demographic and medical history data collected during the screening period may be used as baseline data

**Table 2 Tab2:** Schedule of activities for sites

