### Assessment and data collection

Demographic data will include age, sex, race, and ethnicity. Medical history will capture comorbid conditions and clinically relevant diagnoses requiring pharmacological treatment within 1 year prior to enrollment. Laboratory assessments will include serum potassium, UACR, and eGFR, with UACR calculated from measured urinary albumin and creatinine concentrations.

Patterns of RAASi use will be documented, including whether therapy was initiated or continued and, where applicable, the specific drug name, dosage, frequency, start and end dates, and any dose modifications or interruptions, together with the underlying reasons. Pharmacological treatments for hyperkalemia will be recorded in a similar manner, including treatment details and reasons for discontinuation or interruption. Non-pharmacological hyperkalemia management strategies will also be documented, including the intervention type, start and end dates, and reasons for any changes or discontinuation. Clinical progression and medical events will include kidney-specific composite outcomes (sustained eGFR decline ≥ 50%, ESRD, or renal-related death), cardiovascular-specific composite outcomes (rhHF, heart failure-related emergency visits, or cardiovascular death), as well as arrhythmias, hospitalizations, emergency dialysis visits, and death from other causes. In addition, the hyperkalemia management status of each participating site will be assessed using a site-level questionnaire administered at baseline and at weeks 48 and 96 following enrollment of the first patient (Table 2).

Safety will be monitored throughout the study period. A comprehensive baseline assessment will be conducted for each participant, including demographic characteristics, medical history, electrocardiograms, laboratory parameters, vital signs, height, weight, and physical examination findings. During the study, vital signs, electrocardiograms, and laboratory assessments will be performed according to the schedule specified in Table 1. AEs, SAEs, and concomitant medication use will be continuously monitored and systematically recorded. Each reported SAE will be individually reviewed to assess its potential impact on participant safety and the overall conduct of the study. Cumulative AEs will be tracked throughout the study, and all AEs will be followed until resolution, stabilization, or completion of the end-of-study visit.

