### Statistical plans

All statistical analyses will be performed using SAS software (version 9.4 or later). Analyses will be primarily descriptive in nature and will be conducted using non-missing data only.

Except for safety analyses, all efficacy and exploratory analyses will be performed in the full analysis set (FAS), which includes all patients who meet the inclusion and exclusion criteria, unless otherwise specified. Continuous variables will be summarized using the number of observations, mean, standard deviation, median, first and third quartiles, minimum, and maximum. Categorical variables will be summarized as frequencies and percentages. 95% confidence intervals (CIs) will be reported where appropriate. For time-to-event endpoints, analyses will include the number and proportion of patients experiencing each event, along with the corresponding event rates. Kaplan-Meier methods will be used to estimate and graphically present cumulative incidence for both composite and individual endpoints. Changes in eGFR over time will be evaluated using a mixed-effects model for repeated measures (MMRM) to estimate the eGFR slope over the study period.

Safety analyses will be conducted in the safety analysis set (SAS), which includes all patients who have received at least one potassium-binding therapy. The number and proportion of patients experiencing at least one AE, SAE, or ADR will be summarized. Vital signs at each scheduled assessment, as well as findings from physical examinations, electrocardiograms, and laboratory evaluations, will be summarized using descriptive statistics.

A total of four interim analyses are planned, including one primary analysis. The primary analysis is scheduled to occur 48 weeks after enrollment of the final patient.

In addition, predefined subgroup analyses will be performed for the primary and selected secondary endpoints. Subgroups will be defined based on demographic characteristics, baseline disease features (including baseline eGFR to reflect CKD stage), geographic region, and other clinically relevant factors such as history of heart failure, diabetes mellitus, RAASi use, and hyperkalemia treatment patterns.

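### The heart-specific composite (secondary endpoint 10) has two different component lists, and its hospitalization component is worded as rehospitalization with no index admission named

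*Protocol article*

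**What the plan says.** The composite is described in three places in the protocol article.

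- Endpoints, item (10), takes the earliest event in "the heart-specific composite endpoint, including rehospitalization for heart failure (rhHF), worsening heart failure, emergency room visits, or cardiovascular death".
- Table 1, footnote o, under Timeline of the study, has "Cardiovascular-specific composite events: rhHF, worsening HF, emergency room visit, or cardiovascular death".
- Assessment and data collection has "cardiovascular-specific composite outcomes (rhHF, heart failure-related emergency visits, or cardiovascular death".

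The abbreviation list under Table 1 expands the first component as "rhHF, rehospitalization for heart failure", in agreement with item (10).

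Emergency visits also appear outside the composite. Footnote o continues with "Other events: arrhythmia, hospitalization, emergency dialysis, emergency department visit, and death due to other causes", and secondary endpoint (13) is "the proportion of patients requiring emergency department visits, emergency dialysis, or hospitalization during the 48-week intervention period".

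The eligibility criteria summarized under Participants do not mention heart failure. Statistical plans names it only as a subgroup variable, among "other clinically relevant factors such as history of heart failure".

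**The concern.** Two of the three descriptions attach no cause to the emergency visit and list worsening HF separately. The third restricts the visit to HF and leaves worsening HF out. These are different endpoints, and because both are printed, this is not detail that an article leaves to a fuller document. Whoever writes the analysis specification has to choose, and the article does not say which list governs.

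Footnote o adds to the difficulty. It puts an emergency room visit inside the cardiovascular composite and an emergency department visit in its residual category, with nothing to tell a site which heading a given visit belongs under.

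The term rehospitalization presupposes an earlier admission, but no section says which one. Patients without prior HF can evidently enrol, since HF history is a subgroup variable.

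The study aims to provide evidence on long-term cardiorenal benefit. With a single arm, the absolute incidence of this composite is the result itself, and there is no comparator in which the same definition would apply to both sides.

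**Working it through.** **Step 1. The component lists side by side.**

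| Component | Endpoints, item (10) | Table 1, footnote o | Assessment and data collection |
|---|---|---|---|
| HF hospitalization | rehospitalization | rhHF | rhHF |
| Worsening HF | listed | listed | not listed |
| Emergency visit | no cause stated | no cause stated | HF-related only |
| Cardiovascular death | listed | listed | listed |

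Item (10) and footnote o agree. Assessment and data collection differs from both in two rows.

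**Step 2. What each list does with the same patient.**

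| First occurrence | Item (10) and footnote o, read literally | Assessment and data collection |
|---|---|---|
| Emergency visit for an injury | event | no event |
| Worsening of known HF, no admission or emergency visit | event | no event |
| First HF admission through an HF emergency visit | event (emergency visit) | event (emergency visit) |
| First HF admission, direct, HF already known | not rhHF; possibly worsening HF | no event unless cardiovascular death follows |
| First HF admission, direct, new-onset HF | not rhHF; doubtful as worsening HF | no event unless cardiovascular death follows |

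The first two rows follow from the contradiction. The last two follow from the word rehospitalization, taken at face value.

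**Step 3. Size.** The article gives no event rate, count or precision for this composite, so there is no figure of the plan's to reproduce. Its only precision figure, 3.4%, belongs to the primary endpoint and does not depend on this definition.

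What can be given is the condition under which the emergency component would matter most. Let c be the rate of the HF and cardiovascular-death components and e the rate of emergency visits unrelated to HF, both per patient-year. Assume both are constant and that c is the same before and after such a visit, and ignore dropout and other deaths. Item (10) is followed to week 96 ("The maximum duration of follow-up will be 96 weeks"), so T = 96/52 = 1.846 years.

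- Share of first events that are visits unrelated to HF: e/(c + e). This exceeds one half exactly when e > c.
- Cumulative incidence with HF-related visits only: 1 − exp(−cT).
- Cumulative incidence with any emergency visit: 1 − exp(−(c + e)T).

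With an assumed c = 0.06, the restricted composite has incidence 1 − exp(−0.06 × 1.846) = 10.5%. Adding visits unrelated to HF:

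| Assumed e | Incidence, any emergency visit | Share of first events unrelated to HF |
|---|---|---|
| 0.05 | 1 − exp(−0.11 × 1.846) = 18.4% | 0.05/0.11 = 45% |
| 0.10 | 1 − exp(−0.16 × 1.846) = 25.6% | 0.10/0.16 = 63% |
| 0.20 | 1 − exp(−0.26 × 1.846) = 38.1% | 0.20/0.26 = 77% |

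Over c from 0.03 to 0.10 and e from 0.05 to 0.40, the share runs from 33% (0.05/0.15) to 93% (0.40/0.43). The width of that range shows how little can be said without rates.

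**The case against.** The strongest answer is that HF-related visits were meant throughout. Assessment and data collection says so outright. Footnote o lists emergency department visits separately, which would be redundant if the composite already took every visit. A comma may also have split a single component, worsening HF leading to an emergency visit, into two. This is the more likely intention, and it supports the direction of the fix. It does not remove the contradiction: the endpoint definition itself carries no restriction, and a programmer would work from that.

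Second, the endpoint is one of 18 secondary items in a primarily descriptive study, and Statistical plans provides Kaplan-Meier estimates for individual as well as composite endpoints. The mix of events would therefore be partly visible. This stands and limits the severity.

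Several stronger readings are tempting but not supported:

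- A reader might infer that the composite will be dominated by non-cardiac events. No rates are given, and the figures above depend wholly on assumed inputs. A visit unrelated to HF is also not always non-cardiac; one for arrhythmia is an example.
- A reader might infer that first HF admissions are excluded altogether. The word rehospitalization limits one component only, and other components can capture some first admissions.
- A reader might take this as the only cardiac outcome. Endpoint (11), time to first arrhythmia, is another.
- A reader might object that emergency visits are counted twice because endpoint (13) includes them. Overlap between separately reported descriptive endpoints is not an error.

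**Conclusion.** The point stands as an inconsistency of moderate severity. As printed, endpoint (10) cannot be computed reproducibly: its result depends on which section is followed, for the cause of the emergency visit and for worsening HF. The literal endpoint text admits non-cardiac emergency visits as heart events. The rehospitalization wording leaves the handling of a first HF admission unsettled, with the clearest gap for a direct admission with new-onset HF.

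The contradiction rests on the text alone and needs no assumption. Its numerical effect cannot be derived from the article; the only general statement is that visits unrelated to HF would form the majority of first events if their rate exceeded the combined HF and cardiovascular-death rate. The primary endpoint and the sample size are unaffected.

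**What to change.** - Use one component list in Endpoints item (10), Table 1 footnote o, and Assessment and data collection, with the emergency component restricted to HF-related visits, as the last of these already has it.
- State whether worsening HF is a component in its own right.
- Count hospitalization for HF whether first or repeat, or keep rehospitalization and name the index admission.
- Leave all-cause emergency visits to endpoint (13), and make footnote o say which visits belong to the composite and which to its residual category.
- Confirm that the cause of each emergency visit is recorded. The event form is not shown, so a new field may not be needed.

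The cost is a wording change in three places and fewer composite events, hence a less precise estimate relative to its size. Endpoint (13) covers only 48 weeks, so all-cause visits after that would be reported only as collected events unless its period is extended.

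The change is best made before the composite is tabulated at any of the four planned interim analyses. If the last patient enrolled on January 24, 2026, as Trial status expects, 96 weeks (672 days) run to about November 27, 2027. Events are still accruing, and the cause of a visit is easier to record at the time than to recover later.

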### Intervention

The study will implement a QIP targeting both HCPs and patients, incorporating standardized hyperkalemia management and ongoing quality audits. The methods and processes of the intervention are outlined in Table 3. Core components of hyperkalemia management include a standardized clinical pathway based on guideline-directed medical therapy, encompassing the use of serum potassium > 5.0 mmol/L as the diagnostic criterion, long-term hyperkalemia management strategies, targeted dosing of RAASi, and protocolized serum potassium monitoring at least every 3 months, or monthly in patients at high risk of hyperkalemia, including those with CKD combined with diabetic kidney disease, CKD combined with heart failure, or CKD undergoing initiation or uptitration of RAASi therapy. Both serum potassium testing frequency and RAASi optimization will be systematically tracked throughout the study. The standardized hyperkalemia management protocol for patients with CKD will be implemented as illustrated in Fig. 2, with the tiered management approach detailed in Table 4. The guideline-directed medical therapy framework is informed by the KDIGO 2024 Clinical Practice Guideline for the Evaluation and Management of Chronic Kidney Disease [17], the Expert consensus on the management of serum potassium in chronic kidney disease patients in China (2020) [18], and the Guidelines for the early evaluation and management of chronic kidney disease in China (2023) [19].

**Table 3 Tab3:** Method and process of intervention

	HCP level	Patient level
Hyperkalemia disease management	Key contents: • Follow clinical pathway: hyperkalemia diagnosis >5.0 mmol/L, hyperkalemia long-term management^#^, RAASi targeted dose treatment and serum K^+^ test at least once per 3 months and high-risk cases^*^ once per month • Track serum K^+^ test frequency and RAASi optimization. Quality audit results as feedback for additional education. Frequency: • 1 comprehensive training • 4 mandatory intensive trainings (every 12w with the 1st at week 4) • ≤6 additional intensive trainings if quality audit is off-target	Key contents: • Disease introduction, poor outcomes and the importance of serum K^+^ monitoring Frequency: • 6 sessions of disease and medication adherence education from HCPs during onsite visits; self-learning

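### Secondary endpoint (12) counts high potassium tests rather than episodes, so the raw count rises with testing frequency and can mislead

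*Protocol article*

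**What the plan says.** The Endpoints section defines secondary endpoint (12) as "frequency of serum potassium testing and number of hyperkalemia episodes during the first 48 weeks of intervention (onsite and remote visits". An episode is a result above 5.0 mmol/L, and the only merging rule given is "multiple measurements within 48 h counted as a single episode".

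The Intervention section sets "protocolized serum potassium monitoring at least every 3 months, or monthly in patients at high risk of hyperkalemia". It adds that "Both serum potassium testing frequency and RAASi optimization will be systematically tracked throughout the study", and Table 3 feeds audit results back into further training.

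Under Timeline of the study, "each participant will attend six scheduled onsite visits at weeks 12, 24, 36, 48, 72, and 96 post-enrollment", so four onsite visits fall in the 48-week window. The notes to Table 1 describe the contacts between them: "Telephone calls will be conducted every 4 weeks (± 7 days) following enrollment if no onsite visit occurs". On these calls patients are reminded to follow their clinician's advice on potassium testing. The call itself includes no test.

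The Statistical plans section foresees subgroup analyses of the primary and selected secondary endpoints, including by heart failure, diabetes and RAASi use. It does not name the secondary endpoints selected.

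**The concern.** An episode should be a period of raised potassium with a beginning and an end. Under the stated rule it is any result above 5.0 mmol/L that is more than 48 h from another. A patient whose potassium stays high from day 1 to day 30 and who is tested on days 1, 5 and 30 has three episodes, although nothing resolved or recurred.

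That would matter little if everyone were tested equally often. Here testing differs by design between risk groups, tests between onsite visits depend on clinician and patient, and the programme audits and trains for adequate testing. The quantity that the programme tries to raise is thus the one that inflates the count. A patient or site that follows the monitoring pathway closely can show more hyperkalemia than one that does not, with no difference in potassium. The groups assigned monthly testing also overlap the planned heart-failure, diabetes and RAASi subgroups.

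**Working it through.** **The plan's own figure.** The article gives no figure for the episode count. Its one design figure is the precision of the primary endpoint, 3.4% (Sample size estimation). With 1,000 × (1 − 0.20) = 800 evaluable patients, 1.96 × √(0.45 × 0.55 / 800) = 0.0345. This agrees with the stated figure and does not bear on this point.

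**Inputs**
- Window: 48 weeks (endpoint 12).
- Tests k: quarterly 48/12 = 4, monthly 48/4 = 12 (Intervention; a month taken as 4 weeks). The quarterly figure is a minimum.
- Probability p that a test exceeds 5.0 mmol/L: not in the document. Assumed range 0.10 to 0.55.

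**Expected count.** Scheduled tests are all more than 48 h apart, so none are merged, and expected episodes = k × p.

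| p (assumed) | Quarterly, 4p | Monthly, 12p | Ratio |
|---|---|---|---|
| 0.10 | 0.4 | 1.2 | 3.0 |
| 0.20 | 0.8 | 2.4 | 3.0 |
| 0.30 | 1.2 | 3.6 | 3.0 |
| 0.40 | 1.6 | 4.8 | 3.0 |
| 0.55 | 2.2 | 6.6 | 3.0 |

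The ratio is 12/4 whatever p is. Only the absolute counts depend on the assumption.

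**One unbroken elevation.** Twelve weeks above 5.0 gives 12/12 = 1 episode with quarterly tests and 12/4 = 3 with monthly tests.

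**Break-even.** For a patient moved from quarterly to monthly testing, the count falls only if 12 × p(new) < 4 × p(old), that is p(new) < p(old)/3. The chance of a high result per test must drop by more than two thirds.

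**Simulation check.** Daily potassium was simulated for 20,000 patients over 336 days (assumed: mean 4.6 to 5.0, between-person SD 0.3, within-person SD 0.4, autocorrelation time 7 or 30 days). The same curves were then sampled on each schedule.
- With about 21% of time above 5.0: 0.84 episodes from 4 tests, 2.53 from 12, about 5.05 from 24.
- With about 34% of time above 5.0: about 1.37, 4.12 and 8.25.
- Episodes per test were the same on all schedules (about 0.21 and 0.34).

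**Does an intervening normal value cure it?** In part. With that rule the same simulations give, monthly against quarterly, ratios from 2.09/1.05 = 2.0 to 1.66/0.61 = 2.7. These runs count a high first follow-up test as a new episode. In a second simulation all patients entered above 5.0, that elevation was treated as still running, and test-to-test noise was independent (mean 4.9, SDs 0.40 and 0.30). It gave 1.67/0.45 = 3.7. The rule lowers the counts in all of these runs, but in none does it remove the dependence on testing.

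**The case against.** Four points can fairly be made for the plan.

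1. *Testing frequency is reported in the same endpoint.* True, and it lets a careful reader see the problem. It does not correct the count, and no per-test rate is stated.

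2. *Potassium control is judged elsewhere.* This stands. The primary endpoint is fixed at week 48, and endpoint (1) gives the proportion with normokalemia at each onsite visit. Endpoint (1) is close to a fixed-visit measure of burden, though it also counts values below 3.5 mmol/L as failures. The issue is confined to a secondary endpoint.

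3. *No comparison is planned that the count could bias.* This largely stands. The study is single-arm and descriptive. No pre-programme episode count and no comparison of episodes between sites is described, and subgroup analysis of endpoint (12) is only possible. A reader might infer that better monitoring will look like worse control. The document supports only that it can: treatment under the pathway could lower p enough to outweigh extra tests.

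4. *The fourfold-against-twelvefold contrast is not firm.* This stands in part. Quarterly testing is a floor. The Intervention text names RAASi initiation or uptitration as high risk, while the Table 3 footnote names CKD on RAASi. Who is tested monthly is thus unsettled, and the passages must be reconciled. The actual ratio may differ from 3.0, but the count would still follow the tests performed.

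A reader might also infer that the 48 h rule distorts endpoint (6), "time to first hyperkalemia recurrence". The rule stands only inside endpoint (12), and the article does not extend it. How recurrence is made operational may be left to the full protocol or analysis plan, so no fault follows there.

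**Conclusion.** The point holds for endpoint (12). The stated rule makes the episode count a count of positive tests more than 48 h apart. With identical potassium control, monthly testing yields three times the episodes of quarterly testing. That ratio follows from the schedule alone, whereas the absolute counts rest on assumed probabilities of a high result and on simulations without a treatment effect. Raw counts can therefore mislead when read across patients, across sites, or across the heart-failure, diabetes or RAASi subgroups if endpoint (12) is among those selected.

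This is a defect in a stated definition, not a detail left to the analysis plan. It is worth correcting before the 48-week primary analysis, but it does not touch the primary endpoint or endpoint (1).

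**What to change.** For endpoint (12):

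- Take as the main measure of burden the number of scheduled onsite visits (weeks 12, 24, 36, 48) with potassium above 5.0 mmol/L, shown with the number of those visits that have a result.
- If episodes are kept, start a new one only after an intervening value of 5.0 mmol/L or below, and state how the elevation present at enrolment is treated.
- Report episodes per test performed beside the count.
- State two limits. The per-test rate is still affected if high values prompt retesting. The intervening-value rule alone reduces the dependence on testing but does not remove it (monthly-to-quarterly ratio about 2.0 to 2.7, or 3.7 in the second simulation, all under assumed values).

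The cost is a change of definition, slightly more analysis work and a less simple count. No new data are needed.
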